**Aims and hypotheses**
Aim 1: the first aim is to evaluate the implementation effectiveness of digital peer support training between emerging adults providing support (befrienders) and emerging adults seeking help (seekers).Research question 1a: is Acceset digital peer support training an effective training curriculum in providing peer support?Hypothesis 1a: the digital peer support training is effective for befrienders in providing peer support, as demonstrated by the adoption of and fidelity to the training curriculum.Research question 1b: is the Acceset text-based intervention (ie, the platform) feasible and acceptable (ie, safe and timely) as an ongoing mechanism of support for seekers and befrienders?Hypothesis 1b: digital peer support is feasible and acceptable in offering support for emerging adults’ mental well-being, which is evidenced by 2 indicators:The engagement of the seeker-befriender-moderator interaction across the 4 time points—baseline (before the intervention), 3 weeks (conclusion of the intervention), and 6 and 9 weeks (carryover effect assessment)—that is indexed by the waiting period for seekers to receive a response. Delays are defined as a >48-hour waiting period and will be categorized based on the following reasons: (1) technical factors (eg, the befriender is not able to log into the platform to respond in time) and (2) human factors (eg, the befriender drops out from the study, and no replacement is found in time). An acceptable response time is within 48 hours, and this is emphasized during Acceset digital peer support training for befrienders [37].The use of technical features of the Acceset platform that is measured by the seeker dropout rate at each stage of engagement with the Acceset platform, the number of visits on the study registration website, the number of participants who registered with Acceset, the average number of letters exchanged, and the average number of emotion and functional adjustment stickers and motivation graphic interface formats used [37].Research question 1c: is the Acceset text-based intervention (ie, the platform) feasible and acceptable (ie, safe and timely) as an ongoing mechanism of support that identifies individuals who are at an unacceptably high risk of mental health conditions?Hypothesis 1c: digital peer support is feasible and acceptable in offering support for emerging adults’ mental well-being by identifying individuals who are at an unacceptably high risk of mental health conditions related to depression and suicidality, which is measured before and during engagement based on 3 means—specifically, the Acceset algorithm detection of the content of the letters, the moderators’ vetting of the content of seekers’ letters, and the seekers’ self-report responses to the 9-item Patient Health Questionnaire [38] (refer to the Implementation Outcomes section for details [37]).Aim 2: the second aim is to elucidate whether Acceset digital peer support harnesses the 4 components of emerging adult mental health—mattering, selfhood, compassion, and mindfulness.Research question 2a: does Acceset digital peer support enhance the 4 components among seekers and befrienders?Hypothesis 2a: Acceset digital peer support (training) increases the 4 components among befrienders (before and after training) and seekers (over the course of the study across 4 time points).Research question 2b: is Acceset digital peer support effective in improving emerging adult mental well-being?Hypothesis 2b: digital peer support leads to significantly better mental well-being of seekers compared with the control group. This effect is sustained beyond the period of the intervention.Aim 3: the third aim is to investigate the mechanism of change in emerging adult mental well-being involving digital peer support (delivered by the Acceset platform).Research question 3: what is the mechanism explaining the change in emerging adult mental well-being involving digital peer support?Hypothesis 3: the initial level and rate of change (ie, growth factors) of befrienders’ web-based support positively predict the growth factors of seekers’ psychological well-being in accordance with latent growth curve modeling.

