Upon recruitment, seekers will be able to register in two ways: (1) by engaging with a Telegram chat channel, an instant messaging app that allows users to send text messages, photos, videos, stickers, and files, which is a prevalent mode of communication among young people, and (2) through the Acceset website. The user will provide their email address, password, age, and gender. When using Telegram, the seekers will submit consent to the privacy policy and terms of use and acknowledgment that they fulfill the criteria for research participation (being aged 19-25 years and having no clinically diagnosed mental illnesses). During the intervention, seekers will be able to anonymously share their emotional experiences by writing e-letters. In response, they will receive support from a peer (befriender) who has received Acceset digital peer support training. When using the Acceset website, an automated bot will function as a courier to deliver the letter to the Acceset platform. The chatbot will also inform the user when they have a letter in the mailbox. The user will log in to retrieve the response letter from their mailbox.

The letter exchange will be monitored by moderators—certified counselors with the required background and assessment tools to identify seekers at risk of depression and suicidality. These moderators have received certified trainings that are accredited by the Australian, New Zealand, and Asian Creative Arts Therapies Association and Swinburne University of Technology in Professional Counselling; have a master’s degree in Social Science; and are certified by the Ministry of Education, Singapore, and the Executive Counselling and Training Academy to provide holistic counseling for students and supervision for counselors. Professionally, these moderators are experienced counselors at various IHLs; serve as vice-presidents of the Singapore Association for Counselling; and partner with schools and the Health Promotion Board, Singapore, to provide a range of counseling services to emerging and working adults.

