Befriender engagement will be monitored, and they will receive a reminder email after 48 hours if there is no reply to the seeker. A questionnaire battery over 4 time points will be used to monitor befrienders and seekers (Multimedia Appendix 3). These time points will include baseline (before the intervention), 3 weeks (end of the intervention), and 6 and 9 weeks (carryover effect measurement; Figure 1) [37]. Signals for closure will be done through an email reminder sent 7 days before the conversation ends, and another email will be sent to inform seekers and befrienders when the thread officially closes after 21 days. Where there are issues that reflect high negativity and suicidal thoughts and expressions at any point in the letter thread, we will immediately link the seekers to the appropriate professional counseling resource.

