#### Implementation Outcomes

For research question 1a and hypothesis 1a, we will determine whether Acceset digital peer support training is an effective curriculum for befrienders in providing effective peer support. We will assess the adoption of and fidelity to the training curriculum through the letter exchanges between seekers and befrienders. The text of the letter exchanges will be evaluated in terms of the extent to which befrienders display fidelity in applying the 4 components of psychological well-being in response to seekers’ disclosure. All correspondence will be anonymized before analysis, and the seekers’ letters will only be used to provide content for the befrienders’ responses. With respect to research question 1b, hypothesis 1b, research question 1c, and hypothesis 1c, we will evaluate the feasibility and acceptability of sustaining access to web-based peer support in terms of (1) initial and sustained engagement of seekers, befrienders, and moderators (ie, certified counselors); (2) the use of technical features of the Acceset platform; and (3) the identification of participants with high risk of mental health conditions relating to depression and suicidality.

This study will assess the waiting period for a seeker to receive a response. Delays (defined as a >48-hour waiting period) will be categorized based on the following reasons: (1) technical factors (eg, the befriender is not able to log into the platform to respond in time) and (2) human factors (eg, the befriender drops out from the study, and no replacement is found in time). An acceptable response time is within 48 hours, and this is emphasized during Acceset digital peer support training for befrienders. The seeker dropout rate at each stage of engagement with the Acceset platform will be assessed based on (1) the number of visits to the study registration website, (2) the number of participants who registered with Acceset, (3) the average number of letters exchanged, and (4) the average number of emotion and functional adjustment stickers and motivation GIFs used.

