#### Mechanism of Action

For research question 3 and hypothesis 3, we will elucidate the mechanism of change that links digital peer support intervention to emerging adult mental well-being (Figure 3). Specifically, we will assess whether and how the level at the start of the study and the rates of change from baseline to weeks 3, 6, and 9 in befrienders’ support relate to seekers’ mental well-being.

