Latent growth curve modeling (LCM) will investigate the mechanism of change involving the trajectories of peer support in predicting the change in psychological well-being [59]. LCM delineates whether and how the exposure to the intervention changes over time with psychological outcomes by estimating and comparing different baseline latent growth models, including linear, quadratic, and nonlinear curve fitting (ie, optimal fit). In other words, LCM elucidates whether the trend in befrienders’ peer support predicts the trend in seekers’ psychological well-being (Figure 3). Current research assessing peer support intervention for the mental health of young people does not consider the mechanism of change. By establishing a change model, this protocol provides a basis for building the therapeutic potential of digital peer support that harnesses the components of emerging adult mental well-being to reduce psychological symptoms. Specifically, LCM elucidates whether and how the intervention affects the development of psychological symptoms and how they unfold over time among emerging adults. This finding provides actionable knowledge for timely and relevant digital peer support.

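### The slope-on-slope path in Hypothesis 3 covers one and the same interval for befriender and seeker, so it cannot show which drives the other and should be reported as an association, not as the mechanism of change

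*Protocol article*

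**What the plan says.** Textbox 1 gives Aim 3 as finding the mechanism of change. Hypothesis 3 says that the befrienders' initial level and "rate of change (ie, growth factors) of befrienders’ web-based support positively predict the growth factors of seekers’ psychological well-being". The Discussion repeats it.

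The Mechanism of Action section sets the time frame. Besides the starting level of support, it will assess how "the rates of change from baseline to weeks 3, 6, and 9 in befrienders’ support relate to seekers’ mental well-being". Participants and Study Setting puts both parties on one schedule: "A questionnaire battery over 4 time points will be used to monitor befrienders and seekers".

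Data Collection, Management, and Analyses names latent growth curve modelling and describes its purpose as trend on trend: "LCM elucidates whether the trend in befrienders’ peer support predicts the trend in seekers’ psychological well-being". The same paragraph then gives the causal reading: "LCM elucidates whether and how the intervention affects the development of psychological symptoms and how they unfold over time among emerging adults". It adds that the finding can be acted on.

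Four further statements bear on direction:
- Support is a reply to what the seeker writes: "In response, they will receive support from a peer (befriender) who has received Acceset digital peer support training" (Participants and Study Setting).
- The letter thread ends after 21 days (same section).
- Befrienders pick the seekers they prefer to support (Peer Emotional Disclosure).
- Control seekers are wait-listed for the platform (Participants and Study Setting).

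**The concern.** A positive path from the support slope to the well-being slope is what the article would count towards Hypothesis 3. The two slopes are estimated over the same nine weeks, so neither precedes the other. The same data would arise if seekers who were improving for other reasons drew more, or better, support from their befrienders. That route is plausible here because support is reactive by design, and it would exist even if pairs were formed at random.

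Randomisation does not settle it. Variation in support among arm 1 seekers is not randomised, and controls have no befriender during the comparison. None of the sections that state or interpret Hypothesis 3, nor the limitations, mentions direction.

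At stake is one of the three aims. A slope-on-slope association could be presented as evidence of how peer support changes symptoms when the data cannot separate that from the reverse.

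**Working it through.** The article gives no effect size, SD or power for Hypothesis 3, so there is no figure of its own to reproduce. From the document: 50 arm 1 seekers, waves at weeks 0, 3, 6 and 9, two-sided .05, letters only within 21 days. All other inputs below are assumptions.

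**Step 1: direction.** With one predictor, the test of a slope on a slope is t = r√(n−2)/√(1−r²). This depends only on the correlation r and is the same whichever variable is the outcome. With n = 50 and the mean observed correlations at a true slope correlation of 0.5:
- seeker drives support, r = 0.319: t = 0.319 × 6.928/0.948 = 2.33
- support drives seeker, r = 0.320: t = 0.320 × 6.928/0.947 = 2.34

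Simulation: 3,000 trials per setting, four equally spaced waves, slope SD 0.3 per wave, residual SD 0.5, and least-squares slopes per pair as an approximation to the growth model. Share of trials with a significant positive path from befriender slope to seeker slope:

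| True slope correlation | Seeker drives support | Support drives seeker |
|---|---|---|
| 0.3 | 27.5% | 27.2% |
| 0.5 | 64.0% | 64.5% |
| 0.6 | 81.0% | 80.9% |
| 0.7 | 91.8% | 91.2% |

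With no link the share is 2.6%. At 0.6 the mean coefficients are 0.388 and 0.389. The planned path does not distinguish the two cases.

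**Step 2: size, which depends on when support can react.** Let support have no effect on the seeker but react to the seeker's current state with strength b. Centred times are −4.5, −1.5, 1.5 and 4.5, with sum of squares 45, so the least-squares slope weights are −0.100, −0.033, 0.033 and 0.100. If intercept and slope are independent, the covariance of the seeker's week-3 state with the seeker's slope is 3 × Var(slope). The covariance induced between the two slopes is then:
- reaction at all four waves: b × Var(slope)
- reaction at week 3 only: −0.033 × b × 3 × Var(slope) = −0.1 × b × Var(slope)
- week-3 reaction carried unchanged to weeks 6 and 9: (−0.033 + 0.033 + 0.100) × b × 3 × Var(slope) = 0.3 × b × Var(slope)

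Simulated false confirmation (nominal 2.5%), with intercept SD 1, reliability 0.85, b = 0.3 to 0.7 and seeker slope SD 0.06 to 0.15 per week:

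| When support reacts | Slope SD 0.10 | All settings |
|---|---|---|
| Week 3 only | at or below about 2.5% | at or below about 2.5% |
| Week-3 reaction persists | about 5–16% | about 5–33% |
| All four waves | 22%, 59%, 94% (b = 0.3, 0.5, 0.7) | about 10–100% |

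A separate run of the middle row gave 3–35% over all settings.

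**Step 3: a time-ordered alternative.** Regressing a later seeker score on support during the thread, adjusted for baseline and week-3 scores, gave about 5–37% false positives in the same simulations. Adjustment for a week-3 score measured with error is incomplete, so the bias is reduced but not removed.

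**The case against.** The strongest objection concerns the timetable. A reader might infer that false confirmation is common, at the rates in the bottom row of the table, because letters are replies. The documents do not support that. Baseline precedes any contact and the thread ends after 21 days, so letters cannot supply support scores at four waves. The statement that "befrienders display fidelity in applying the 4 components of psychological well-being in response to seekers’ disclosure" belongs to the training-fidelity outcome of Hypothesis 1a, not to the Hypothesis 3 predictor. Support may instead come from the four-wave questionnaire battery, which would make the reverse route less direct. This stands: no single rate can be given.

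The sign of the reaction is also assumed. Befrienders might give more support as seekers worsen, which would bias against Hypothesis 3. Each befriender serves 3 seekers, so a befriender-level score would dilute any reaction to one of them. Both points stand.

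A reader might also infer that the article commits itself to reporting reactive support as a cause. That is too strong. Hypothesis 3 says predict, and Mechanism of Action says relate. The causal reading sits in Aim 3 and the analysis section. Hypothesis 3 also contains the initial-level path, whose predictor precedes later seeker change.

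Finally, model detail may sit in an analysis plan that is not shown. That is so, but the hypothesis, the common time frame and the interpretation are all fixed in this article, and the point rests on those.

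**Conclusion.** The point holds in a limited form. The slope-on-slope part of Hypothesis 3 is a same-interval association in a non-randomised comparison, and it fits equally well in either direction. It cannot by itself establish the mechanism of change or show how the intervention affects symptoms.

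The conclusion about direction needs no assumed reaction strength. The size does: from no inflation to nearly 100%, according to whether support reacts at week 3 only, persists, or tracks the seeker throughout. Those figures use least-squares slopes in place of the growth model and ignore shared befrienders, so they show sensitivity and do not predict what this trial would find.

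It would be wrong to conclude that the effectiveness result is compromised. Hypothesis 2b rests on the randomised arms and is unaffected. Nor does the point require Hypothesis 3 to be dropped or its test replaced.

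**What to change.** In Textbox 1, Mechanism of Action, and Data Collection, Management, and Analyses, describe the slope-on-slope path as an association between concurrent trends. Remove the wording that presents it as the mechanism or as the effect of the intervention. Keep the initial-level path.

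Add a time-ordered model, labelled as supporting: support scored during the 21-day thread predicts seekers' week 6 and week 9 scores, adjusted for baseline and week-3 scores, with the reverse path reported beside it.

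The rewording costs almost nothing. The added model uses letters and questionnaires that the study already collects. The Results section says that data collection had ended and analysis had begun, so the model should be declared as added at that stage. It has two drawbacks: it misses change that is complete by week 3, and it still carried about 5–37% false positives in the simulations. It should not be called proof of mechanism either.

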
## Methods

### Trial Design

This trial is registered with the US National Library of Medicine ClinicalTrials.gov (NCT05083676). We are initiating an interventional prospective study with a hybrid design that evaluates both the implementation of the Acceset intervention (eg, fidelity, adoption, and utility) and participant outcomes (eg, anxiety and depressive symptoms) via a randomized controlled trial (RCT). The intervention comprises 2 components—digital peer support training and a digital text-based intervention (ie, the platform)—involving 3 features: digital markers of psychological well-being, the peer emotional disclosure process, and community engagement.

### Participants and Study Setting

We plan to recruit 130 participants (100 seekers and 30 befrienders) at the National University of Singapore (NUS) to engage with the Acceset intervention in accordance with an Institutional Review Board–approved protocol. Participants will be recruited via the Research Participation program within the Department of Psychology at NUS, where students will be awarded credits as part of the introductory courses for psychology. During recruitment, inclusion and exclusion criteria screening will be conducted via self-reporting. Participants qualified for inclusion (seekers) will be randomized into 2 arms. The seekers (n=50), befrienders (n=30), and moderators (n=30) in arm 1 will use Acceset for 3 weeks. The control group (n=50) in arm 2 will be wait-listed for Acceset use. It should be noted that the wait-listing approach is a standardized approach for RCTs pertaining to digital mental health [37,39,40].

We will recruit age- and gender-matched individuals from NUS. The 4–time-point questionnaire battery of arm 1 will be used to compare the mental well-being and help-seeking behavior with those in arm 2 [37]. Moderators will be recruited from the Singapore Executive Counselling and Training Academy. If an unacceptably high risk of depression and suicidality is detected at any time point by the moderator, who is a certified counselor, they will reach out to the participant, who will be directed to different clinical mental health support providers, including counseling centers and hotlines, on the NUS campus. On the basis of power analysis and the finding that 20% to 40% of the emerging adults enrolled in an IHL typically experience distress, this sample will provide a sufficiently powered comparator group.

Upon recruitment, seekers will be able to register in two ways: (1) by engaging with a Telegram chat channel, an instant messaging app that allows users to send text messages, photos, videos, stickers, and files, which is a prevalent mode of communication among young people, and (2) through the Acceset website. The user will provide their email address, password, age, and gender. When using Telegram, the seekers will submit consent to the privacy policy and terms of use and acknowledgment that they fulfill the criteria for research participation (being aged 19-25 years and having no clinically diagnosed mental illnesses). During the intervention, seekers will be able to anonymously share their emotional experiences by writing e-letters. In response, they will receive support from a peer (befriender) who has received Acceset digital peer support training. When using the Acceset website, an automated bot will function as a courier to deliver the letter to the Acceset platform. The chatbot will also inform the user when they have a letter in the mailbox. The user will log in to retrieve the response letter from their mailbox.

The letter exchange will be monitored by moderators—certified counselors with the required background and assessment tools to identify seekers at risk of depression and suicidality. These moderators have received certified trainings that are accredited by the Australian, New Zealand, and Asian Creative Arts Therapies Association and Swinburne University of Technology in Professional Counselling; have a master’s degree in Social Science; and are certified by the Ministry of Education, Singapore, and the Executive Counselling and Training Academy to provide holistic counseling for students and supervision for counselors. Professionally, these moderators are experienced counselors at various IHLs; serve as vice-presidents of the Singapore Association for Counselling; and partner with schools and the Health Promotion Board, Singapore, to provide a range of counseling services to emerging and working adults.

The moderation protocol at the participant recruitment stage entails the screening of seekers using a validated psychological scale—the 9-item Patient Health Questionnaire (PHQ-9)—to exclude individuals at high risk of depression and suicidality. During the intervention phase, befrienders are also trained to alert moderators when seekers are at an unacceptably high risk of depression and suicidality, and the moderator vets all the letter exchanges between the seekers and befrienders for content of high negativity and suicidal thoughts and expressions. This moderation protocol aims to identify seekers who are at an unacceptably high risk of depression and suicidality and refer them to an appropriate mental health care provider, including counseling centers and hotlines, on the NUS campus.

Each befriender will provide support to 3 seekers, receive notification from the Acceset platform on incoming letters, and work in partnership with the moderators to address the seekers’ issues during the 3 weeks of letter exchange. Befrienders have the choice to discontinue the letter exchange with seekers if they feel discomfort having to address issues that they find challenging by informing trained moderators. Given the sensitive nature of the letter content, there may be issues that befrienders will be exposed to that they are not fully comfortable with and may cause distress. Therefore, it is a deliberate design to ensure that the befrienders are not left on their own in handling cases and that they work in partnership with the 2 trained and certified moderators to address the seekers’ issues. The first point of contact for the befriender will be the 2 trained and certified moderators. In such cases, the befriender’s workload decreases to 2 seekers.

The system will inform the seeker and obtain their consent to continue the conversation with a new befriender or end the letter thread. If the seeker chooses to continue, the system will notify all befrienders of the availability of an ongoing case, and interested befrienders can take it up. In addition, other trained befrienders (whom Acceset has trained beyond the recruited 30 befrienders for this study) will be activated to take up the case if no existing befrienders take it up. Similarly, when befrienders drop out of the study during the 3 weeks of letter exchanges, they will be replaced with other trained befrienders. Befrienders’, seekers’, and moderators’ use of the Acceset platform is to remain completely anonymous such that the 3 parties do not have direct contact with one another, and seekers do not have discretion to switch befrienders on their own. In the event of disagreement between seekers and befrienders (eg, seekers are concerned with how their issues are not adequately addressed during the letter exchange), they will be able to notify the study team. The system will inform the seeker and obtain their consent to continue the conversation with a new befriender or end the letter thread. If the seeker chooses to continue, the system will notify all befrienders of the availability of an ongoing case, and interested befrienders can take it up. However, it should be noted that such situations will be rare given that moderators will vet all letter exchanges and work in partnership with befrienders to ensure that their responses are satisfactory. If seekers drop out of the study, their befrienders will continue with the reduced workload.

Befriender engagement will be monitored, and they will receive a reminder email after 48 hours if there is no reply to the seeker. A questionnaire battery over 4 time points will be used to monitor befrienders and seekers (Multimedia Appendix 3). These time points will include baseline (before the intervention), 3 weeks (end of the intervention), and 6 and 9 weeks (carryover effect measurement; Figure 1) [37]. Signals for closure will be done through an email reminder sent 7 days before the conversation ends, and another email will be sent to inform seekers and befrienders when the thread officially closes after 21 days. Where there are issues that reflect high negativity and suicidal thoughts and expressions at any point in the letter thread, we will immediately link the seekers to the appropriate professional counseling resource.

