The following approaches will be used for data analysis and interpretation. Independent-sample 2-tailed *t* tests will compare the intervention and control groups. Bonferroni post hoc tests will control for multiple comparisons. For both the intervention and control groups, additional independent *t* tests will compare seekers who provided data across all 4 time points with those who dropped out from the study for different reasons to ascertain if the sample with data across all 4 time points and the sample with fewer data points bias our results. For instance, seekers may drop out when risk assessments identify them as having a high risk of depression and suicidality during the course of the study. There will also be instances when befrienders discontinue the letter writing because of the sensitive nature of the letter content that may cause distress and befrienders not being fully comfortable, and the system will inform the seekers and obtain their consent to end the letter thread instead of continuing the conversation with a new befriender. Second, each participant’s emotional experiences disclosed on Acceset will be extracted based on the definitions of the 4 components of psychological well-being. Latent Dirichlet allocation analyses in R (R Foundation for Statistical Computing) and content analysis will be used [37,60,61].

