## Results

This protocol received approval from the Institutional Ethics Review Board of NUS in October 2021. Recruitment will commence in January 2022. Data collection began in March 2022 and was completed in June 2022. Data analysis started in July 2022 and is currently in progress. We aim to report the preliminary study outcomes in December 2022. The effect size will be analyzed using the Cohen *d* index with a significance level of .05 (95% reliability) and 80% power statistic [37]. A total of 100 seekers, 35 befrienders, and 2 moderators were recruited in January 2022.

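### Some arm 1 seekers share a befriender, but the arm comparison is a t test that assumes independence; the effect is small to modest, and the befriender and moderator counts need reconciling

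*Protocol article*

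**What the plan says.** Participants and Study Setting describes the delivery of arm 1: "The seekers (n=50), befrienders (n=30), and moderators (n=30) in arm 1 will use Acceset for 3 weeks". It adds "Each befriender will provide support to 3 seekers" and "the moderator vets all the letter exchanges between the seekers and befrienders". For arm 2 it says "The control group (n=50) in arm 2 will be wait-listed for Acceset use", so no control seeker has a befriender or a moderator during the comparison.

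Data Collection, Management, and Analyses fixes the test: "Independent-sample 2-tailed *t* tests will compare the intervention and control groups". Bonferroni tests are added for multiple comparisons. Neither that section nor the power statements mention clustering, an ICC, a design effect or a befriender term. The latent growth curve model serves Aim 3 and is not described as adjusting the arm comparison.

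The staffing figures differ by place:
- The Abstract and the start of Participants and Study Setting give 30 moderators.
- Later in Participants and Study Setting, befrienders are told that "they work in partnership with the 2 trained and certified moderators to address the seekers’ issues", and "The first point of contact for the befriender will be the 2 trained and certified moderators".
- Results reports "A total of 100 seekers, 35 befrienders, and 2 moderators were recruited in January 2022".

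**The concern.** Seekers who write to the same befriender receive a common part of the treatment. Hypothesis 3 (Aims, Research Questions, and Hypotheses) states that the level and trend of befrienders' support predict seekers' well-being. If that is so, outcomes of seekers with the same befriender are correlated after randomisation, in arm 1 only. The t test treats 50 arm 1 seekers as 50 independent observations. Its confidence intervals would be somewhat too narrow and its p values somewhat too small for inference beyond the particular befrienders recruited.

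The conflicting counts matter to the same question. The number of seekers per befriender sets the cluster size, and the number and deployment of moderators decide how far the result depends on very few people.

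**Working it through.** **Inputs from the article.** 50 seekers per arm; 30 befrienders planned, 35 recruited; three seekers per befriender; significance level .05 and two-sided t tests; 80% power. **Assumed:** befriender ICC of 0.05, 0.10 or 0.20 (none is stated), and equal total variance in both arms.

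**1. The plan's own sample size.** No effect size or SD is given, so 50 per arm cannot be reproduced. Inverted under independence, it corresponds to d = (1.960 + 0.842) × √(2/50) = 0.56.

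**2. Places against seekers.** 30 × 3 = 90 places (35 × 3 = 105) for 50 arm 1 seekers. At three each, 17 befrienders suffice (16 × 3 + 1 × 2 = 50). Spread evenly, 30 befrienders have 50/30 = 1.67 seekers each on average. Even with all 35 in use, 50 seekers exceed 35 befrienders, so some sharing is unavoidable.

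**3. Effective cluster size**, m = Σ(size²)/Σ(size):
- 35 befrienders, even load (15 with two, 20 with one): (60 + 20)/50 = 1.60
- 30 befrienders, even load (20 with two, 10 with one): (80 + 10)/50 = 1.80
- 17 befrienders with up to three each: (144 + 4)/50 = 2.96

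**4. Effect on the t test.** Arm 1 design effect DE = 1 + (m − 1) × ICC. Because only arm 1 is clustered, correct SE / t test SE = √((1 + DE)/2). Actual two-sided error = 2 × [1 − Φ(1.96 / SE ratio)].

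| Load | ICC | DE | SE larger by | Type I error | Power at d = 0.56 |
|---|---|---|---|---|---|
| 35, even | 0.05 | 1.030 | 0.7% | 5.2% | 79% |
| | 0.10 | 1.060 | 1.5% | 5.3% | 79% |
| | 0.20 | 1.120 | 3.0% | 5.7% | 78% |
| 30, even | 0.05 | 1.040 | 1.0% | 5.2% | 79% |
| | 0.10 | 1.080 | 2.0% | 5.5% | 78% |
| | 0.20 | 1.160 | 3.9% | 5.9% | 77% |
| 17, three each | 0.05 | 1.098 | 2.4% | 5.6% | 78% |
| | 0.10 | 1.196 | 4.8% | 6.1% | 76% |
| | 0.20 | 1.392 | 9.4% | 7.3% | 73% |

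The power column uses the corrected SE. Simulated error rates of the t test agree with the formula to within about 0.2 percentage points.

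**5. Topic matching.** Under Peer Emotional Disclosure, befrienders choose seekers by the topic of the letter. To see whether this alone inflates the error, 51 v 51 seekers were simulated, with arm 1 sorted by topic into threes and no befriender effect (40,000 trials per setting). The observed within-befriender ICC was about 0.10 or 0.20, yet the t test's error stayed between 4.8% and 5.1%. A cluster-adjusted SE gave 4.0% and 3.2%, which is conservative.

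**6. Moderators, conditional only.** If two moderators held separate caseloads of 50/2 = 25, a moderator ICC of 0.01, 0.02 or 0.05 would give DE = 1.24, 1.48 or 2.20 and error of 6.4%, 7.8% or 12.1%. If both serve all arm 1 seekers, their effect is common to the arm. There is then no within-arm correlation to correct, and the effect cannot be told apart from the intervention.

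**The case against.** Four points can be made for the plan.

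*The effect is small.* This stands for an even load: at ICC 0.05 to 0.10 the standard error is only 0.7% to 2.0% too small. Loads of three, which the article itself describes, raise that to 2.4% to 4.8%.

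*If the intervention affects nobody, befrienders induce no correlation and the t test keeps its level.* This stands. The inflation concerns inference across befrienders whose effects vary around a mean of zero. It does not arise under a strict null in which no seeker is affected.

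*Matching by topic makes seekers of one befriender alike.* A reader might infer that this worsens the problem. It does not: seekers are randomised individually and sorted afterwards, which leaves the variance of the arm mean unchanged (step 5). It does mean that a befriender random effect may absorb some harmless similarity and so be slightly conservative.

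*Two moderators would push the false-positive rate to 12% or more.* A reader might infer this from the count of two. The article does not support it, because no section allocates seekers to moderators. The references to befrienders working with the two moderators, and to those two as the first point of contact, read at least as naturally as joint moderation.

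Nor do 90 places for 50 seekers prove an error in design. Three may be a maximum load, and the article provides for reduced loads when a befriender stops an exchange or a seeker drops out.

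An analysis plan that is not shown does not remove the point, because the article names a specific test that conflicts with its own delivery structure.

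**Conclusion.** The point holds in a limited form. Sharing of befrienders in arm 1 is certain if the stated numbers are right, and the named test ignores it. Under assumed ICCs of 0.05 to 0.20, the standard error is too small by between 0.7% (35 befrienders, even load, lowest ICC) and 9.4% (three each, highest ICC), and the two-sided error lies between about 5.2% and 7.3%. This is worth correcting because it is cheap to do, but it does not threaten the trial. The size rests on the assumed ICC, on equal total variances and on how seekers were distributed, none of which the article gives.

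The contradiction between 30 and 2 moderators is a separate point and needs no assumption. With two, a moderator variance can hardly be estimated, and the moderators' effect cannot be separated from that of the intervention. Any moderator-level error rate should be quoted only as conditional on separate caseloads.

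**What to change.** 1. Replace the t test for the arm comparison with a partially nested mixed model: a random effect for the first-assigned befriender in arm 1 only, controls as singletons, a separate residual variance for each arm, and Satterthwaite degrees of freedom.
2. Add a sensitivity analysis for seekers who changed befriender, since the article allows replacement during the three weeks.
3. Restate the power with an assumed range of ICCs.
4. Reconcile the moderator count between the Abstract, Participants and Study Setting, and Results. Reconcile the befriender load with 50 arm 1 seekers, and say whether three is a maximum. State whether the moderators share all letters or hold separate caseloads.
5. If there are two moderators, limit conclusions to delivery under those two.

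The cost is analysis code, the seeker-befriender link for each arm 1 seeker, and corrected text. Questionnaires and letters are stored against participant IDs, so the link should be recoverable, and Results describes the analysis as still in progress. Intervals become slightly wider, and possibly a little conservative where topic matching accounts for part of the within-befriender similarity.
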